## Abstract

**Background:**

There is a robust empirical evidence base supporting the acute efficacy of electroconvulsive therapy (ECT) for severe and treatment resistant depression. However, a major limitation, probably contributing to its declining use, is that ECT is associated with impairment in cognition, notably in anterograde and retrograde memory and executive function. Preclinical and preliminary human data suggests that ketamine, used either as the sole anaesthetic agent or in addition to other anaesthetics, may reduce or prevent cognitive impairment following ECT. A putative hypothesis is that ketamine, through antagonising glutamate receptors, protects from excess excitatory neurotransmitter stimulation during ECT. The primary aim of the ketamine-ECT study is to investigate whether adjunctive ketamine can attenuate the cognitive impairment caused by ECT. Its secondary aim is to examine if ketamine increases the speed of clinical improvement with ECT.

**Methods/Design:**

The ketamine ECT study is a multi-site randomised, placebo-controlled, double blind trial. It was originally planned to recruit 160 moderately to severely depressed patients who had been clinically prescribed ECT. This recruitment target was subsequently revised to 100 patients due to recruitment difficulties. Patients will be randomly allocated on a 1:1 basis to receive either adjunctive ketamine or saline in addition to standard anaesthesia for ECT. The primary neuropsychological outcome measure is anterograde verbal memory (Hopkins Verbal Learning Test-Revised delayed recall task) after 4 ECT treatments. Secondary cognitive outcomes include verbal fluency, autobiographical memory, visuospatial memory and digit span. Efficacy is assessed using observer and self-report efficacy measures of depressive symptomatology. The effects of ECT and ketamine on cortical activity during cognitive tasks will be studied in a sub-sample using functional near-infrared spectroscopy (fNIRS).

**Discussion:**

The ketamine-ECT study aims to establish whether or not adjunctive ketamine used together with standard anaesthesia for ECT will significantly reduce the adverse cognitive effects observed after ECT. Potential efficacy benefits of increased speed of symptom improvement and a reduction in the number of ECT treatments required will also be assessed, as will safety and tolerability of adjunctive ketamine. This study will provide important evidence as to whether adjunctive ketamine is routinely indicated for ECT given for depression in routine NHS clinical practice.

**Trial Registration:**

Current Controlled Trials: ISRCTN14689382 (assigned 30/07/2012); EudraCT Number: 2011-005476-41

## Background

Depression is a leading cause of disability worldwide with unipolar depression ranked 9^th^ in the world and 3^rd^ in Europe amongst causes of health-related disability 2000–2012 [1] and at any one time around 3 % of the UK population meet the criteria for major depression [2]. Effective treatment remains a major problem in depression; in the largest study to date examining patient outcomes in major depression, the STAR*D study, only a quarter to a third of patients remitted after the first antidepressant and a about third had still failed to remit after 4 drug interventions [3].

The National Institute for Health and Clinical Excellence (NICE) recommends electroconvulsive therapy (ECT) as a treatment option for patients with severe depression that is life threatening or those with moderate or severe depression who have not responded to multiple drug treatments and psychological treatment [4]. ECT has been demonstrated to have greater efficacy than pharmacotherapy (effect size, ES -0.8) [5] and achieves remission rates of about 50 % in patients who have failed to respond to drug treatments [6]. It has equal efficacy in both unipolar and bipolar depressed patients [7].

Despite the robust evidence base demonstrating the efficacy of ECT, the number of patients being treated with it has fallen dramatically in recent decades. In England over a 3 month period in 2006, an estimated 1250 patients received ECT compared with over double that number in 1999 [8]. The reduction in ECT usage may be a consequence of concerns about a poor riskbenefit balance due to adverse cognitive side effects [9]. ECT treatment is associated with significant objective impairments in cognitive function, the largest effect being on verbal delayed recall, but also with significant impairment in all tests of anterograde memory, executive function and processing speed [10]. Following the end of ECT treatment there is a rapid reversal of deficits, with moderate to large improvements above baseline in most measures after 1–2 weeks [10]. However, one study showed enduring deficits in spatial recognition memory one month after end of treatment [11]. There is uncertainty as to the magnitude and persistence of retrograde amnesia following ECT [12], though a systematic review suggested that 29–55 % of patients reported persistent and often distressing loss of important past memories after ECT [13]. It has been reported that there is an association between subjective memory impairment and objective autobiographical memory impairment immediately after ECT course as well as 6 months later [14]. A survey across multiple clinical hospitals suggested that the severity, incidence and persistence of memory and cognitive dysfunction after ECT was related to treatment approach [15].

The precise mechanisms underlying the effects of ECT are not fully understood, but altered synaptic functioning in neural circuits involved in mood and cognition is thought to play a key role [16]. Glutamate, an amino acid neurotransmitter with a role in both neuroplasticity and excitotoxicity, acts on a variety of receptors in the brain, most commonly N-methyl-d-aspartate (NMDA) and α-amino-3-hydroxy-5-methylisoxazole-4-propionic acid (AMPA) receptors [17]. Preclinical evidence supports a role for glutamate in mood regulation and in the action of antidepressant treatments [17, 18]; in particular decreased NMDA-mediated, and increased AMPA-mediated neurotransmission has been proposed [18]. Studies in depressed patients have found decreased frontal cortical measures of glutamate measured in vivo by magnetic resonance spectroscopy (MRS) which normalises with effective treatment [17]. There are similar findings with ECT; pre-treatment glutamate and glutamate-related concentrations have been found in dorsolateral prefrontal cortex [19] and anterior cingulate cortex [20, 21] which either normalised after ECT [19, 21] or predicted treatment response [20].

Glutamate also has a central role in cognition especially learning and memory, through its role in synaptic plasticity and the signalling pathway involved in long-term potentiation in the hippocampus [22]. It has been proposed that the memory impairment occurring with ECT is a consequence of indiscriminate activation/saturation of glutamate receptors at the time of the seizure leading to a disruption of hippocampal plasticity involved in memory [23]. Autobiographical memory impairment may occur through disruption of the reconsolidation of ‘fragile’ reactivated or recalled memories [24].

Ketamine is a dissociative anaesthetic, analgesic and psychotomimetic which inhibits NMDA receptors but also stimulates glutamate release and potentiates activity at non-NMDA receptors such as AMPA receptors [25]. Recent studies have shown a rapid antidepressant effect after a single dose of intravenous ketamine alone or as an adjunct to antidepressants in both unipolar and bipolar depression [26]. Repeated administration maintains improvement but relapse occurs rapidly on stopping treatment [27]. Side effects of ketamine treatment include acute anxiety, increased mood instability, vomiting, and vasovagal episodes, dissociation, dry mouth, tachycardia and increased blood pressure [27], though more severe cardiovascular side effects are associated with higher ketamine doses (0.8–1.0 mg/kg) [26].

Given acutely ketamine can cause cognitive impairment [28], particularly in manipulating information in working memory and encoding into episodic memory. However, preliminary human data from retrospective/non-randomised studies suggested that ketamine anaesthesia improves reorientation [29, 30] and word recall [31] after ECT, and also may result in more rapid clinical response [32]. Subsequent small randomised controlled trials (RCTs) have produced mixed results with studies suggesting impaired reorientation [33, 34] and improved [35] or unchanged [33] Mini Mental State Examination (MMSE) scores after ketamine. A further study found that ketamine augmentation produced no reduction in cognitive impairment after ultra-brief right unilateral stimulation on a range of tests [36]; however this technique is associated with minimal cognitive impairment compared with standard bilateral ECT which limits interpretation. Two recent meta-analyses looking at efficacy, and including the same 4 placebo-controlled RCTs in which ketamine has been combined with ECT, have reached different conclusions. When continuous measures were pooled a moderate to large advantage for ketamine was reported early in the ECT treatment course [26], but no benefit was found when end-of-treatment response and remission were meta-analysed [37]. The latter meta-analysis also reported higher rates of confusion/disorientation/prolonged delirium with ketamine. At present the small heterogeneous studies of ketamine augmentation of ECT emphasise the need for further larger scale trials.

Depression is associated with impaired frontal cortical metabolism and function [38, 39] and treatment with antidepressant drugs leads to their normalisation [38, 40]. In contrast ECT is associated acutely with a further decrease in frontal cortex metabolism [41], and one hypothesis is that the cognitive deficits seen with ECT may relate to these frontal effects [42]. If ketamine prevents cognitive deficits with ECT then a test of this hypothesis is whether ketamine prevents ECT-induced suppression of frontal cortical function.

### Aims and Hypotheses

The primary aim of the Ketamine-ECT study is to investigate the effect of adjunctive ketamine on cognitive dysfunction caused by ECT using an RCT design with the hypothesis that ketamine, compared with saline treatment, given together with standard anaesthesia will reduce ECT-induced cognitive impairment. Secondary aims are to 1) investigate the efficacy, tolerability and acceptability of adjunctive ketamine (we hypothesise that ketamine treatment will lead to a more rapid improvement in depressive symptoms with fewer ECT treatments needed to achieve remission) and 2) to identify whether ketamine modifies ECT’s effect on frontal cortical function using functional near infrared spectroscopy (fNIRS) during performance of cognitive tasks.

## Methods/Design

### Study Design

The Ketamine-ECT study is a randomised, parallel group, placebo-controlled, double blind trial of ketamine (0.5 mg/kg), compared to saline, added to standard anaesthetic induction, in depressed patients who have been prescribed ECT. Both participants and researchers will be blinded to the treatment arm to which patients are allocated. In the interests of patient safety, the anaesthetic team will be aware of study treatment allocation, with this information disclosed to other clinical or research team members only if safety concerns arise.

### Study Population

The study will recruit hospital in-patients and out-patients with moderate to severe depression who have been prescribed ECT by their treating psychiatrist and have been determined fit for ECT and ketamine administration by an anaesthetist. All participants will provide written informed consent. The original aim was to recruit 160 patients, however due to slow recruitment a revised target of 100 patients, and refinement of the primary outcome measure, together with a study extension, was agreed between the study team, Data Monitoring and Ethics Committee (DMEC) and Trial Steering Committee (TSC), Research Ethics Committee, the Medicines and Healthcare products Regulatory Authority (MHRA), the funder and the sponsor. The recruitment target for a sub-population drawn from those taking part in the main RCT to undergo mechanistic studies was originally 100 (revised to 20 due to slow recruitment) together with 50 matched healthy volunteers recruited for neuropsychological and fNIRS baseline testing comparisons.

#### Patient Inclusion criteria

Male or Female aged 18 years and above prescribed ECT by their treating psychiatrist.Current Diagnostic and Statistical Manual of Mental Disorders-Fourth Edition (DSM-IV) diagnosis of a major depressive episode, moderate or severe, as part of unipolar or bipolar disorder, diagnosed using the Mini International Neuropsychiatric Interview (MINI) [43].American Society of Anesthesiologists score of 1, 2 or stable 3 (excluding mental health considerations in the scoring), and judged as suitable to receive ketamine by an anaesthetist.Verbal IQ [44] equivalent to 85 or greater and sufficiently fluent in English to validly complete neuropsychological testing.Capacity to provide written informed consent to take part in the study.

#### Patient Exclusion criteria

DSM-IV diagnosis of a primary psychotic or schizoaffective disorder, current primary obsessive compulsive disorder or anorexia nervosa.History of drug or alcohol dependence (DSM-IV criteria) within the last year.ECT in last 3 months or has previously received ECT in the current trial.Known hypersensitivity or contraindication to ketamine or excipients in the injection, including significant cardiovascular disease, uncontrolled hypertension, glaucoma, cirrhosis or abnormal liver function or liver disease.Known hypersensitivity or contraindication to concomitant medications used for ECT including propofol or suxamethonium or excipients in the injections.Evidence of organic brain disease including dementia, neurological illness or injury, or medical illness which may significantly affect neuropsychological function.Detained under the Mental Health Act (1983 as amended 2007).Pregnancy, or at risk of pregnancy and not taking adequate contraception, breastfeeding.Score of less than 24 on the MMSE [45].

Psychotropic medication-free healthy volunteers without a personal or family history of major psychiatric illness or significant medical illness will also be recruited. They will be aged over 18 years or over and will be matched as a group with patients for age and sex.

### Recruitment

Patient recruitment was originally planned for 6 NHS Trusts in the North of England. This was subsequently increased to 7 Trusts, with 11 ECT suites. Recruitment for the fNIRS mechanistic sub-study, including healthy volunteers, will be based in two of the centres where the equipment will be based (Manchester and Newcastle), with opportunity to recruit from other sites when practically feasible to transport the equipment to patients.

### Intervention

ECT and anaesthetic treatment protocols will be determined by the local ECT services but is required to be consistent with requirements given in the Royal College of Psychiatrists’ ECT handbook [46]; ECT being given twice a week. The anaesthetic induction agent of choice is propofol, with thiopental permissible as an alternative. For safety reasons etomidate cannot be used to avoid the potential for an interaction with ketamine excessively elevating blood pressure. Oral psychotropic medication continued by the patient’s treating clinical team will remain unchanged where possible for at least the first 4 ECT treatments, and ideally until end of ECT. The goal of ECT is to treat patients to remission (Montgomery-Åsberg Depression Rating Scale, MADRS ≤10) in accordance with NICE guidelines [4]. The final decision to end ECT will rest with the treating clinical team in consultation with the patient and the local ECT treatment team. Following recruitment, and before their first ECT treatment, patients will be randomised in a 1:1 ratio to receive ketamine 0.5 mg/kg or saline as a slow bolus before the anaesthetic induction agent. Randomisation will be by permuted block randomisation, stratified by NHS Trust, carried out by the Manchester Academic Health Science Centre Clinical Trials Unit (http://www.mahsc-ctu.co.uk/). Randomisation will occur by telephone and allocation communicated securely to each Trust Pharmacy which will securely over-package the study drug to conceal allocation. On the day of each treatment the anaesthetist will open the package and prepare the injection away from the ECT team and patient to maintain their blinding. Patients will receive the same allocated study medication throughout their course of ECT.

### Outcome measures

All assessments will be undertaken by trained research personnel under the supervision of the clinically trained principle investigators. Figure 1 shows the study schedule for visits and assessments. The primary outcome time point will be after the fourth ECT treatment.

**Fig. 1 Fig1:**
[figure not shown]
Flowchart of schedule of visits. fNIRS: function near infrared spectroscopy; MINI: Mini International Neuropsychiatric Interview; Observer ratings: Breif Psychiatric Rating Scale; Montgomery Åsberg Depression Rating Scale; Clinical Global Impression; Self ratings; EuroQol; Quick Inventory of Depressive Symptomatology-Self Report

#### Neuropsychological measures

The Hopkins Verbal Learning Test-Revised (HVLT-R) [47] will be used as the primary outcome measure to assess anterograde memory. Secondary measures are described in Table 1. The cognitive assessment battery has been shown in previous research to be sensitive to the effects of ECT [36] and has been chosen to also be short enough in duration to be acceptable to patients.

**Table 1 Tab1:** Description of neuropsychological and clinical efficacy outcome measures

Abbreviation	Full Name	Description	Reference
Neuropsychological Measures			
HVLT-R	Hopkins Verbal Learning Test – Revised	Anterograde verbal learning and memory assessment	[47]
AMI-SF	Autobiographical Memory Inventory – Short Form	Retrograde assessment of personal memories	[59]
COWAT – letter and category	Controlled Oral Word Association Test	Letter and Category fluency assessment	[60]
MCG – Complex Figure Test	Medical College of Georgia Complex Figure Test	Anterograde visuospatial memory assessment	[61]
Digit Span	Digit Span	Working memory assessment	[62]
GSE-My	Global Self-Evaluation of Memory	Self-reported assessment of memory	[63]
Reorientation	Reorientation	Number of 5 orientation items correct 30 and 60 min after ECT	[64]
Clinical Efficacy Measures			
MADRS	Montgomery-Åsberg Depression Rating Scale	Observer-rated assessment of depressive symptoms	[48]
CAS	Clinical Anxiety Scale	Observer-rated assessment of anxiety symptoms	[65]
BPRS	Brief Psychiatric Rating Scale	Observer-rated assessment of psychiatric symptoms	[66]
CGI-S, CGI-I	Clinical Global Impression – Severity and Improvement	Observer-rated global measure of illness severity and improvement	[67]
QIDS-SR	Quick Inventory Depressive Symptomology – Self Rated	Self-rated measure of depressive symptoms	[68]
EQ-5D	EuroQol	Self-rated measure of health-related quality of life	[69]

#### Clinical efficacy measures

The primary efficacy measure will be change in MADRS score [48] from baseline with secondary outcomes listed in Table 1.

#### Mechanistic measures

Bilateral dorsolateral and ventrolateral prefrontal cortex response to computerised tasks of verbal fluency (for category) and working memory (N-Back) will be measured using fNIRS, a portable brain imaging technique that can be used at the bedside or in a person’s home. This uses the differential light absorption properties of oxyhaemoglobin (HbO) and deoxyhaemoglobin (HbR) for near infrared light when it passes through the scalp, skull and superficial layers of the cortex from a light source placed on the scalp. The change in the light absorption spectra are measured with detectors placed nearby also on the scalp. The technique is analogous to functional magnetic resonance imaging (MRI) using blood oxygen level dependent changes, although it measures both HbO and HbR. It is possible to use fNIRS as a measure of functional changes in cortical blood flow secondary to neuronal activation [49].

In addition, a spatially resolved spectroscopy technique will be used, employing a modification of the diffusion equation of light transport, to provide an absolute measure of tissue oxygenation (the tissue oxygenation index). This index is the absolute percentage of total haemoglobin in the field of view which is oxygenated [50]. Its reliability and validity has yet to be established [51], however it does provide a potential absolute measure with which to assess cerebral tissue metabolism across groups and within subjects [52].

Two purpose built optical tomography systems (Biomedical Optics Research Laboratory, Dept. of Medical Physics and Bioengineering, University College London) provide a 48 channel array for topographical coverage of bilateral dorsolateral and ventrolateral prefrontal cortices.

Originally it had been planned to undertake glutamate magnetic resonance spectroscopy and structural and functional MRI in a subgroup, but this had to be halted when it became clear that insufficient patients would be recruited to allow valid analysis.

### Sample size, power and effect size

#### Original sample size and power calculation

Across the 6 NHS Trusts originally involved in the study, 355 patients received ECT over a 12 month period in 2009/10, the most recent period available when planning the study. The most comparable recent study in the UK [53] found that 41 % of patients receiving ECT were eligible, using similar inclusion/exclusion criteria to ours, and 18 % were randomised (to either ECT or transcranial magnetic stimulation). Given the current study offers adjunctive, rather than alternative treatment, a 22.5 % recruitment rate was predicted. Based on these figures recruitment of 160 patients over a 24 month recruitment period was forecast as feasible, providing 152 patients for primary end point assuming 95 % of patients can be assessed after 4 treatments.

The power calculation was based on a clinically useful benefit of a moderate standardised effect size (ES) for the ketamine-saline difference (0.5–0.6). With a 90 % power, and two-sided *p* = 0.05, based on independent t-tests, we would have been able to detect a standardised ES of 0.51 for full Intention-To-Treat (ITT) and 0.54 for a single primary cognitive outcome based on completer assessments. Using a Bonferroni correction for the originally proposed three measures for the primary cognitive outcome, HVLT-R, COWAT category and AMI-SF (i.e., assuming independence) gives an 80 % power to detect a standardised ES of 0.51 given a two-sided, corrected, *p* = 0.05 for each measure.

The study aimed to recruit 100 patients (50 per treatment group) and 50 matched healthy controls to the mechanistic studies. This would have an 80 % power to detect an ES of 0.5 with a two-sided alpha level of 0.05 between groups and an ES of 0.57 with a two-sided alpha level of 0.05 between treatment arms. A previous fNIRS study in depressed patients [54] found an ES difference from controls of 0.8 in frontal cortex HbO response to a verbal fluency task.

#### Revised Power calculations

Following initial slow recruitment, the revised recruitment target was adjusted to 100 patients with 95 reaching the primary outcome measure point and the primary outcome was changed to the HVLT-R alone. This sample size provides 80 % power to detect an ES of 0.57 (ITT) and 0.58 (completer), two-sided *p* = 0.05. The target for recruitment to the mechanistic studies was decreased to a sample size of 20 patients (10 per treatment arm) and 50 controls. This has only a 21 % power to detect an ES of 0.6 with a two-sided *p* = 0.05 between the two treatment arms (10 per arm). Comparing 20 patients and 50 controls will give an ability to detect an ES of 0.6 between groups with 60 % power and two-sided *p* = 0.05, and a 70 % power to detect the same size of effect of ECT itself with a two-side *p* = 0.05.

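### The 21% power stated for the fNIRS comparison of treatment arms does not follow from its inputs: 10 per arm at an effect size of 0.6 gives about 25%

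*Protocol article*

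**What the plan says.** The Revised Power calculations section says that the mechanistic sub-study target was "decreased to a sample size of 20 patients (10 per treatment arm) and 50 controls". It then gives three power figures, all for an effect size of 0.6 at two-sided 0.05:

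- Ketamine v saline, described as "between the two treatment arms (10 per arm"): "This has only a 21 % power to detect an ES of 0.6".
- Patients v healthy controls: "Comparing 20 patients and 50 controls will give an ability to detect an ES of 0.6 between groups with 60 % power".
- Change with ECT: "a 70 % power to detect the same size of effect of ECT itself".

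This section names no test and states no allowance for loss in the sub-study. The only power method named in the article is in the preceding section, Original sample size and power calculation, where the main-trial figures are "based on independent t-tests". The Mechanistic outcomes section plans a repeated measures analysis of variance for the fNIRS data, but gives no correlation or other quantity that would enter a power calculation.

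**The concern.** Sample size, effect size, significance level and resulting power are all printed together, so the figure can be checked directly. Under the t-test it fails that check. A reader then cannot tell which of the number of patients, the effect size or the power is wrong.

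This has a bearing on the neighbouring figures. If the 21% silently assumes fewer than 20 evaluable patients, the 60% and 70% rest on a different number of patients from the figure beside them, and both would be too high on the smaller number.

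**Working it through.** **Inputs.** From Revised Power calculations: n₁ = n₂ = 10, standardised effect d = 0.6, two-sided α = 0.05. The main trial allocates 1:1 (Abstract, Methods/Design), which agrees with equal arms. The independent t-test is carried over from the original main-trial calculation; this is an assumption, because the revised section names no test.

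**Formula.** For two independent groups, the t statistic has df = n₁ + n₂ − 2 and non-centrality δ = d·√(n₁n₂/(n₁+n₂)). Power is P(|T| > t₀.₉₇₅,df), with T non-central t.

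**The arm comparison.**

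- df = 18, and the critical value is 2.101.
- δ = 0.6 × √(100/20) = 0.6 × √5 = 1.342.
- Upper tail 24.5%, lower tail 0.06%, total **24.6%**. Simulation gives 24.3% to 24.5%.
- Stated: 21%. Difference: 24.6 − 21 = 3.6 points.

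**Does the same method reproduce the article's other revised figures?**

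| Comparison | t-test result | Stated |
|---|---|---|
| 20 v 50, d = 0.6 (δ = 0.6 × √(1000/70) = 2.268, df 68) | 60.9% | 60% |
| Paired, n = 20, d = 0.6 (δ = 0.6 × √20 = 2.683, df 19) | 72.1% | 70% |
| Detectable effect, 50 per arm, 80% power | 0.566 | 0.57 |
| Detectable effect, 47.5 per arm, 80% power | 0.581 | 0.58 |

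The paired row assumes that the effect of ECT is a within-patient change, with 0.6 expressed in standard deviations of that change. Apart from that row, which is about 2 points off and may have been rounded down, the method matches. It is therefore the right benchmark.

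**What would give 21%?**

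| Variant, two-sided 0.05 unless stated | Power |
|---|---|
| 10 v 10, d = 0.54 | 20.8% |
| 9 v 8, d = 0.6 | 21.2% |
| 8 v 8, d = 0.6 | 20.1% |
| 9 v 9, d = 0.6 | 22.4% |
| 10 v 9, d = 0.6 | 23.4% |
| Normal approximation, 10 v 10 | 26.8% |
| Welch test, 10 v 10 (simulation) | 23.9% |
| One-sided t-test, 10 v 10 | 36.2% |
| α = 0.025, 10 v 10 | 16.1% |
| Exact Mann-Whitney, 10 v 10 (simulation) | 21.3% |

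**Consistency of those explanations with the rest of the paragraph.**

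- *17 evaluable patients (9 v 8).* The companion figures become 55.8% (17 v 50) and 64.2% (paired, n = 17), against the stated 60% and 70%.
- *Rank test.* Scaling the sample by the minimum relative efficiency of 0.864 gives 21.6% for the arms, but 54.5% for 20 v 50, against the stated 60%.

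**The case against.** Three points can be made for the plan.

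- **The test is not named here.** The t-test is stated for the main-trial calculation, and the planned fNIRS analysis is a repeated measures analysis of variance. An exact Mann-Whitney test gives 21.3%. A rank test thus cannot be ruled out for this single number. It appears nowhere in the article, however, and the rank adjustment does not fit the 60% alongside. A repeated-measures calculation would need inputs that the article does not give.
- **The other two figures may allow for loss.** Applying the main trial's 95% assessment rate to 20 patients gives 19. Then 19 v 50 has 59.3% power and a paired test on 19 has 69.6%, both close to the stated 60% and 70%. On that reading the arm comparison is 10 v 9 with 23.4%. This narrows the gap to 2.4 points but does not close it, and it would make the corrected figure about 23% rather than 25%.
- **Nothing depends on the figure.** The sample of 20 came from slow recruitment, the stated value errs on the low side, and the Discussion already concedes that power for the ketamine effect in this sub-study will be very low.

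The last point stands in full and limits the importance of the error. The first two leave its cause open, but neither shows that 21% follows from what is printed.

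**Conclusion.** The concern holds, as a minor point. On the printed inputs (10 per arm, effect size 0.6, two-sided 0.05) and an independent t-test with no loss, power is 24.6%, not 21%. The conclusion rests on carrying the t-test over from the original calculation, which the agreement of the neighbouring figures supports. Even with one patient lost it would be 23.4%. The comparison is secondary and remains very underpowered; no sample size, analysis or interpretation changes.

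**What to change.** Replace 21% with about 25%, and name the test (independent t-test, 10 v 10, effect size 0.6, two-sided 0.05, no loss).

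If 21% was meant to reflect expected loss or another method, state the evaluable number or the test instead, and recompute the 60% and 70% figures on the same basis.

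The cost is one number in the text, or one sentence and up to two further numbers if the second route applies. The design and the analysis stay as they are.
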